## Abstract

**Background:**

Worldwide incidence of type 2 diabetes (T2D) is rapidly increasing. Given the numerous negative health consequences associated with T2D, prevention of this disease has become a priority. Lifestyle changes, including regular exercise, can reduce the onset of T2D in those at elevated risk. However, long-term adherence to exercise is often poor in this population. Existing lifestyle interventions targeting exercise are labor intensive and costly for staff and participants. Evidence-informed counseling delivered in a manner that reduces dependence on staff and facilitates self-regulatory skills could alleviate time and financial barriers while promoting independent exercise.

**Objective:**

This protocol outlines the design, recruitment, and proposed analysis of a brief, 2-week evidence-informed exercise counseling intervention combined with either high-intensity interval training (HIIT) or traditional moderate-intensity continuous training (MICT).

**Methods:**

Small Steps for Big Changes is a 2-arm randomized controlled trial that will examine the effectiveness of combining brief exercise counseling with HIIT or MICT on adherence to moderate and vigorous exercise over 1 year. Cardiorespiratory fitness will be assessed at baseline, post intervention (2 weeks), and at 6- and 12-month follow-up. Physical activity behavior will be examined at baseline, post intervention, and 3-, 6-, 9-, and 12-month follow-up. The impact of the intervention on psychosocial outcomes pertinent to exercise adherence will be examined.

**Results:**

Data collection was complete in March 2017. Data analysis is currently underway, and the first results are expected to be submitted for publication in 2019.

**Conclusions:**

The results of this brief intervention have the potential to inform future public health efforts designed to increase exercise in individuals at risk of T2D.

**Trial Registration:**

ClinicalTrials.gov NCT02164474; https://clinicaltrials.gov/ct2/show/NCT02164474 (Archived by WebCite at http://www.webcitation.org/74Hx1ipj6)

**International Registered Report Identifier (IRRID):**

DERR1-10.2196/11226

## Introduction

### Background

Type 2 diabetes (T2D) is one of the fastest growing diseases in Canada, with approximately 60,000 new cases diagnosed each year [1]. Globally, it is estimated that 592 million individuals will be diagnosed with T2D by 2035 [2]. Given the numerous negative health outcomes associated with T2D, including heart disease, retinopathy, cataracts, neuropathies, and kidney failure [3-6], increasing attention has turned to intervening with individuals at increased risk of developing T2D (ie, individuals living with *prediabetes*).

Physical activity has been highlighted as beneficial for preventing the progression of prediabetes to T2D [7,8]. However, individuals at risk for T2D often fail to meet the physical activity guidelines of 150 minutes of moderate-to-vigorous aerobic exercise per week [9,10]. Innovative trials, such as the Diabetes Prevention Program (DPP), have demonstrated that a lifestyle intervention incorporating 150 minutes of moderate-intensity physical activity per week can reduce the progression of prediabetes to T2D by up to 58% compared with a non-exercise control and is almost twice as effective as the leading pharmaceutical intervention [11]. At 7-year follow-up, moderate-to-vigorous physical activity behavior was higher among individuals that completed the Diabetes Prevention Program Outcome Study (DPPOS) compared with an equivalent cohort [12]. The DPP and DPPOS follow-up represented a landmark trial designed to assess the potency of lifestyle modification for the prevention of T2D. The trial involved extensive patient contact and monetary incentives to ensure adherence to the prescribed 150 minutes of exercise per week and dietary and weight loss goals. The cumulative cost of the DPP and DPPOS for the lifestyle intervention group was US $4601 per person [13]. Community sites aspiring to achieve similar rates of adherence to physical activity are likely to be constrained by financial and time burdens associated with implementing (and participating in) the DPP. The intensity and expense associated with the DPP and DPPOS could limit the scalable implementation of such interventions. There is an urgent need for affordable and practical interventions that can be delivered in real-world health care or community settings with similar degrees of effectiveness [14]. *Small Steps for Big Changes* is a brief, evidence-informed lifestyle intervention that seeks to overcome the limitations of feasibility and sustainability in previous interventions with the aim of increasing physical activity adherence in individuals at elevated risk of T2D.

### Promoting Physical Activity Adherence

To increase the potential for long-term behavior change, it is important to target theoretically proposed mechanisms of change and incorporate evidence-based behavior change strategies to maximize potential intervention success. Hardeman et al [15] refer to this as a causal modeling approach to intervention development. Interventions that incorporate psychological theory and empirical evidence about how best to support behavior change have been found to be effective [16,17].

Social cognitive theory (SCT) provides a conceptual framework through which to design physical activity interventions. A key construct of SCT is the confidence in one’s ability to carry out and self-manage behavior (ie, *self-regulatory efficacy beliefs*). Self-regulatory efficacy is essential in promoting long-term engagement in behaviors such as physical activity [18]. Another form of self-efficacy, concurrent self-regulatory efficacy, reflects an individual’s confidence to manage health and life goals simultaneously and has been shown to predict physical activity levels [19]. Self-efficacy has been consistently found to be a significant predictor of the adoption and maintenance of physical activity behavior [20,21] and has been reported as the most influential construct on physical activity behavior change [22]. In relation to T2D, self-efficacy has been shown to increase after free-living exercise interventions [23] and has been found to mediate the relationship between intervention delivery and objectively measured physical activity behavior [24]. In addition, personally held efficacy beliefs influence the outcomes an individual anticipates attaining by engaging in the target behavior [25]. These outcome expectations and the value individuals attach to these outcomes can impact physical activity motivation. Individuals who perceive little value or likelihood of achieving benefits associated with physical activity are less likely to self-manage their behavior [25]. As such, fostering positive beliefs about the outcomes an individual will stand to gain from physical activity, which are of value to the individual, will positively influence motivation.

Given the role of self-efficacy beliefs and outcomes expectations as psychological mechanisms of behavior change, a growing body of research has sought to examine the utility and effects of different behavior change techniques (BCTs) in relation to both social cognitions and thereafter physical activity behavior in individuals at risk of T2D [26-28]. For example, Williams and French [27] reported that action planning, reinforcing effort or progress toward behavior, and providing instruction produced significantly higher self-efficacy and physical activity effect sizes compared with interventions that did not incorporate these techniques. A meta-regression by Michie et al [28] reported that interventions that incorporated self-monitoring and self-regulation techniques were significantly more effective at increasing general physical activity behavior than those that did not include these techniques. In the context of T2D, Cradock et al [29] highlighted 4 BCTs associated with reductions in glycated hemoglobin. These techniques included instruction on how to perform a behavior, behavioral practice rehearsal, demonstration of the behavior, and action planning.

*Small Steps for Big Changes* was developed to target the underlying theoretical- and evidence-informed mechanisms of behavior change within a brief intervention to promote long-term physical activity behavior in individuals at risk of T2D. Findings from a pilot feasibility study provided preliminary evidence that the *Small Steps for Big Changes* intervention protocol resulted in significant increases in self-regulatory efficacy and outcome expectations and a significant increase in purposeful moderate-to-vigorous physical activity (MVPA) 1 [30] and 6 months following the program [31].

### Moderate-Intensity Continuous Training: A Traditional Approach

In addition to consideration of the psychological constructs to be targeted within a physical activity intervention, it is also important to consider the modality of exercise prescribed. Traditionally, individuals at risk of T2D embarking on a new exercise regime are prescribed moderate-intensity continuous training (MICT; eg, steady-state walking), with limited free-living adherence typically reported [11]. Given the low rates of adherence to this exercise prescription [32], alternative training protocols, such as high-intensity interval training (HIIT), are increasingly being explored.

### High-Intensity Interval Training: A New Approach for Individuals With Prediabetes

HIIT has received considerable attention as it elicits positive metabolic and cardiovascular adaptations that are similar, or even superior, to MICT in a variety of populations with lower time commitments [33,34]. Specific to diabetes prevention, a recent meta-analysis demonstrated that HIIT leads to greater improvements in insulin resistance compared with MICT [35]. Given the positive health adaptations, HIIT may represent a promising physical activity strategy for individuals with prediabetes.

HIIT involves brief, repeated bursts of vigorous exercise separated by periods of recovery. In a cross-over study of inactive adults, comparable exercise enjoyment and confidence were found between HIIT and MICT, with a greater proportion of participants reporting a preference to engage in HIIT (62%) over MICT (20%) after a single bout of each exercise modality [36]. Similar results are reported in individuals with overweight and obesity [37-39]. Surprisingly, few studies have examined free-living adherence to HIIT in individuals at risk of T2D, despite the known benefits of HIIT on glucose control in this population [40]. In our previous pilot study of individuals living with prediabetes, participants demonstrated greater free-living adherence to HIIT when compared with MICT 1 month following 10 sessions of supervised training and counseling [30]. In addition, accelerometer analysis of physical activity behavior revealed that participants randomized to the HIIT protocol engaged in significantly more vigorous exercise than those randomized to the MICT protocol. Furthermore, after 6 months of independent exercise, participants in the HIIT condition engaged in significantly more moderate-intensity activity compared with those randomized to MICT [31]. Although these initial findings are promising, further research is needed to confirm these results and determine whether individuals with prediabetes can adhere to HIIT over the *long term* (ie, 12 months). Furthermore, trials with greater power are needed to explore whether psychological responses associated with these modalities of activity impact adherence rates.

### Small Steps for Big Changes Objectives

The objectives of this randomized controlled trial are to:

Compare differences in cardiorespiratory fitness between HIIT and MICT at 6 and 12 months after the intervention.Examine accelerometry-measured purposeful moderate-to-vigorous physical activity in bouts of ≥10 minutes (MVPA10+) and total accelerometer counts throughout the follow-up year (ie, 3, 6, 9, and 12 months) after the HIIT and MICT intervention. Self-reported adherence to HIIT and MICT exercise prescriptions will be collected at 3-, 6-, 9-, and 12-month follow-up.Examine the following psychological outcomes to explore their potential relationship with free-living adherence: task self-efficacy, self-regulatory efficacy, concurrent self-regulatory efficacy, self-monitoring, outcome expectations, exercise enjoyment, and instrumental and affective attitudes. In addition, differences in acute affect, in-task enjoyment, and perceived exertion between HIIT and MICT will be compared.Examine differences in cardiometabolic health markers. Glucose control and insulin sensitivity will be assessed at baseline, post intervention, and at 6- and 12-month follow-up. Body composition will be assessed at baseline, post intervention, and at 12-month follow-up. Differences in average blood glucose levels between conditions will be examined immediately after the intervention in a subsample of participants.

## Methods

### Study Design

*Small Steps for Big Changes* is a 2-arm, parallel group randomized controlled trial comparing adherence to HIIT with MICT in individuals at risk of T2D. This single-center trial will be conducted at The University of British Columbia, Okanagan Campus. The design of the study and flow of participants is described in Figure 1. Participants in both conditions will receive a 2-week supervised physical activity intervention consisting of engagement in their randomized exercise modality and brief, targeted counseling. The physical activity counseling will be identical for both conditions. Follow-up assessments will occur at 3, 6, 9, and 12 months. The trial will aim to recruit 100 participants. The supervised training will be conducted in waves (10 waves with approximately 10 participants per wave). All participants will begin supervised training on a Monday. Reporting of this trial protocol follows the Standard Protocol Items: Recommendations for Interventional Trials statement. Future reporting of the results of this trial will follow the Consolidated Standards of Reporting Trials guidelines [41].

### Participants

The study sample will consist of adults aged between 30 years and 65 years; who are physically inactive (ie, engage in 2 or less bouts of moderate and/or vigorous aerobic exercise per week in the last 6 months, assessed using the Godin Leisure Time Physical Activity questionnaire [42]); have a body mass index (BMI) between 25 kg/m^2^ and 40 kg/m^2^; and are cleared to engage in vigorous exercise (via the Physical Activity Readiness Questionnaire for Everyone [PAR-Q+] or further clearance by physician, if needed [43]).

**Figure 1 figure1:**
[figure not shown]
Flow of participants through the Small Steps for Big Changes program.

### Recruitment and Screening

Participants will be recruited using posters administered in the local community, social media, newspaper advertisements, and word of mouth. Advertisements will invite inactive adults aged between 30 years and 65 years to contact the researchers about potential participation in a lifestyle change program, specifically designed to assist individuals who wish to become regular exercisers. A contact phone number and email address will be provided for individuals to contact the research team. Individuals who contact the research team will be able to ask questions regarding the program, and if wishing to proceed, will be scheduled for a previsit telephone screening interview. Telephone screening will take approximately 30 minutes during which the research coordinator will outline the time commitment of the study; record the participants’ age, current medications, height, and weight (to calculate BMI); and administer verbally and record responses to the Godin Leisure Time Physical Activity questionnaire [42] and the PAR-Q+ [43]. Following completion of the initial screening questions, the research coordinator will inform the individual that he or she is (1) ineligible to participate in the program with reasons provided; (2) may be eligible, however, based on the results of the PAR-Q+ clearance and completion of the Physical Activity Readiness Medical Examination (ePARmed-X+) [43] will be required from the individual’s family physician; or (3) may be eligible for the program and will be invited to the laboratory for final screening. Participants required to obtain medical clearance will be sent the ePARmed-X+ (electronically or via mail) and must have the form completed and signed by their physician. Potentially eligible individuals will be sent an information sheet containing study details and will be informed that final eligibility status will be shared following completion of a baseline assessment to confirm objective height, weight, and activity status.

### Baseline Testing and Randomization

Baseline testing will last approximately 150 minutes. Participants will be provided with a detailed consent form and will be invited to ask any questions. After written consent is obtained, weight, height, and blood pressure will be taken and a 7-day physical activity recall interview [44] will be conducted to confirm eligibility.

Eligible individuals will be stratified based on sex and then randomly assigned to either the HIIT or MICT exercise conditions. An external statistician, who has no other involvement in the trial, will generate random allocation sequences, which will be linked to an interactive Web page. Permuted blocks of random size will be used. Once an individual is identified as eligible, the research coordinator will access the password-protected Web page, and after entering requisite information on patient eligibility and sex, participants will be randomly allocated. Participants and researchers will be aware of group allocation. Following group assignment, participants will have a fasting blood sample taken, consume a 75 g glucose drink as part of a modified oral glucose tolerance test, complete several Web-based questionnaires, have a second blood sample taken 30 minutes following the glucose drink consumption, undergo a body composition scan, and complete a maximal cardiorespiratory fitness test to exhaustion on a cycle ergometer. At the end of the session, participants will be provided with an accelerometer to wear for 7 consecutive days, commencing the day after baseline testing. Participants will be shown how to wear the device and will be instructed to remove the device while sleeping or for water-based activities. In addition, instruction will be provided to remind participants how to correctly wear the accelerometer. Short message service (SMS) text messages or emails will be sent on days 1, 3, and 5 of monitoring to remind participants to wear the device (see Multimedia Appendix 1 for study measures).

A voluntary subsample of 8 to 10 participants per group will return to the laboratory 3 days after the preassessment for insertion of a continuous glucose monitor (CGM). The CGM will be worn for 2 consecutive days, and participants will be provided with a standardized diet. Participants will return after 2 days of wearing the CGM to have the CGM removed. These 2 additional visits to the laboratory will last approximately 30 minutes in total. No sample size calculation will be conducted as this aspect of the study represents an exploratory aim to determine if CGM can be used to detect changes in glucose control in this population.

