#### Primary Outcomes

The primary outcome is cardiorespiratory fitness determined by measuring VO_2_ peak at 6- and 12 months postrandomization. VO_2_ peak will be assessed by a continuous incremental ramp maximal exercise test on an electronically braked cycle ergometer (Lode Excalibur, The Netherlands). Expired gas will be collected continuously by a metabolic cart (Parvomedics TrueOne 2400, Salt Lake City, Utah, USA) that is calibrated with gases of known concentration and a 3.0 L syringe before every test. The test begins with a 4-minute warmup at 30 Watts, after which Watts increase by 1 every 4 seconds (15 Watts per minute). Verbal encouragement will be provided to the participant throughout the test. The test will be terminated upon volitional exhaustion or when revolutions per minute fall below 50. VO_2_ peak is defined as the highest 30-second average for VO_2_ (in L/min and mL/kg/min). Criteria for achieving VO_2_ peak are (1) respiratory exchange ratio >1.15; (2) plateau in VO_2_; (3) reaching age-predicted heart rate (HR) peak (220-age); and/or (4) volitional exhaustion. A Polar chest strap, which is integrated with the metabolic cart and cycle ergometer software (Lode Exercise Manager), will capture HR. HR peak and peak power output will be recorded as the highest values attained in the test. Cardiorespiratory fitness will be assessed at baseline and 6- and 12-month follow-up.

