##### Anthropometric and Demographic Measures

Body mass, height (SECA, 700 SECA Hamburg Germany), waist circumference (measured at the level of the umbilicus), and blood pressure (measured manually using a sphygmomanometer) will be measured in the morning after an overnight fast at baseline, post intervention, and at 6- and 12-month follow-up using standard procedures. Information on ethnicity, household income, marital status, education level, medication history, and current smoking status will be collected at baseline.

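### No masking is described for the staff who run the effort-limited primary fitness test, so uneven verbal encouragement could bias the HIIT-MICT contrast by an unknown amount

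*Protocol article*

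**What the plan says.** Under Baseline Testing and Randomization, the protocol article says: "Participants and researchers will be aware of group allocation". It makes no exception for outcome assessors. The same section places the baseline fitness test after group assignment, when participants "complete a maximal cardiorespiratory fitness test to exhaustion on a cycle ergometer".

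Under Primary Outcomes: "The primary outcome is cardiorespiratory fitness determined by measuring VO_2_ peak at 6- and 12 months postrandomization". On how the test is run: "Verbal encouragement will be provided to the participant throughout the test", and "The test will be terminated upon volitional exhaustion or when revolutions per minute fall below 50". The list of criteria for a peak ends with "reaching age-predicted heart rate (HR) peak (220-age); and/or (4) volitional exhaustion". Read literally, the last item alone can suffice.

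Two other sections might have supplied protection. Intervention Fidelity describes a manual, scripts and checklists for delivering the intervention and for the follow-up contacts, not for fitness testing. Data Management and Quality Assurance says in general terms that physiological measures are made in one laboratory with quality assurance in place; it does not mention masking or encouragement. The article does not say who runs the tests.

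**The concern.** Gas exchange is measured by machine, but the participant decides when to stop, and the peak is the highest 30-second average reached before that. A participant who is urged on harder can record a higher value at the same fitness. The article motivates the trial with an expected advantage for HIIT: the Sample Size section takes roughly twice the gain in VO2 peak as its starting point, and the Introduction cites pilot results on activity and adherence that favored HIIT. A tester who knows the arm may share that expectation, with or without being aware of it.

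Participants and counselors cannot be blinded in an exercise trial. The cycle test, however, is the same in both arms, so its tester could in principle be masked. At stake is the primary contrast itself. Intention-to-treat analysis and multiple imputation do not address measurement bias, and the baseline covariate in the mixed model cannot remove a difference that arises at follow-up.

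**Working it through.** **Inputs from the protocol article.** Sample Size: mean 20.8 and SD 4.0 mL/kg/min, correlation among repeated measures 0.5, target difference 9%, two-sided alpha 0.05, 50 randomized per arm with about 20% loss, so 50 × 0.8 = 40 analysed. Primary Outcomes: "Cardiorespiratory fitness will be assessed at baseline and 6- and 12-month follow-up", which gives three measurements.

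**The plan's own figures.** Target: 0.09 × 20.8 = 1.87 mL/kg/min. The stated 15 per group reproduces. For a within-between interaction with f = 0.24, N = 30, three measurements and r = 0.5, the noncentrality is 0.24² × 30 × 3 / (1 − 0.5) = 10.4 on 2 and 56 degrees of freedom, and power is 0.81. Nothing below changes a sample size.

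**Standard error of the baseline-adjusted arm difference, 40 per arm.**
- One visit: 4 × √(1 − 0.5²) × √(2/40) = 0.775.
- Mean of the 6- and 12-month visits: the variance is 16 × (1 + 0.5)/2 − (16 × 0.5)²/16 = 12 − 4 = 8, so the SE is √8 × √(2/40) = 0.632.

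The Proposed Data Analyses section enters both visits in a mixed model but does not say that they are averaged, so both cases are shown.

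**Assumed bias.** Let encouragement raise VO2 peak by 1-5% more in one arm at follow-up. This range is an assumption. With no true effect, the rejection rate is P(|Z + bias/SE| > 1.96):

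| Assumed differential | mL/kg/min | Share of 1.87 | One visit | Mean of two visits |
|---|---|---|---|---|
| 0% | 0 | 0% | 5% | 5% |
| 1% | 0.21 | 11% | 6% | 6% |
| 2% | 0.42 | 22% | 8% | 10% |
| 3% | 0.62 | 33% | 13% | 17% |
| 5% | 1.04 | 56% | 27% | 38% |

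For the two-visit column, the bias must act in the same direction at both visits.

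**If the same bias also acts at baseline.** The baseline test follows open allocation, so this is possible. The adjustment slope is 0.5, so the adjusted contrast carries b − 0.5b = 0.5b. The two-visit rates at 3% and 5% then fall from 17% to 8% and from 38% to 13%. Conversely, if only the follow-up tests were protected and the baseline bias remained, the contrast would carry 0 − 0.5b = −0.5b: half the bias with the opposite sign. The protection therefore has to cover the baseline test as well.

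**The case against.** The strongest reply has four parts.

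1. **Silence is not evidence.** A reader might infer that encouragement was unstandardised, or that every outcome assessor knew the arm. The documents support neither. The article says that encouragement is given, not that it is unscripted, and an unshown laboratory procedure could contain a script. The allocation sentence speaks of researchers in general, and the tester is not identified. This part stands and limits the claim to a risk. A script alone would still leave open whether the tester knew the arm, since the allocation sentence is unqualified.

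2. **The test has objective features.** There is a fixed 15-watt-per-minute ramp, a calibrated metabolic cart, a cadence limit, a defined 30-second average, and criteria on respiratory exchange ratio (RER) and heart rate. These narrow the room for tester influence. They do not close it, because volitional exhaustion can satisfy the criteria by itself.

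3. **The magnitude is hypothetical.** This stands. No document gives a size or a direction, 5% is more than half of the planned effect, and the two-visit column is the more sensitive one.

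4. **The tests are finished.** The Results section says that data collection was complete in March 2017. This stands too: text that now promised masking or scripting would misdescribe the conduct of the trial unless it had in fact happened.

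Manual blood pressure and waist measurements also depend on the operator, but they are secondary and the point does not need them.

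**Conclusion.** The point holds as a risk of assessor bias in the primary comparison. The article states open allocation for researchers, describes no masked tester, and fixes a primary test in which effort, and therefore encouragement, can affect the result. Adjustment for baseline removes none of a bias that arises only at follow-up, and about half of one that acts equally at baseline when r = 0.5.

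If the differential is 1-5%, acts at follow-up only and runs in a constant direction, the false-positive rate at 40 per arm is 6-27% for one visit and 6-38% for the two-visit mean, instead of 5%. At 1% the effect is negligible; it becomes material at about 2-3% and above. A reader might conclude that the trial is biased toward HIIT. The documents do not support that: they show that the possibility was left open, not that it happened or which arm it would favor.

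**What to change.** **As a rule for the test procedure:**
- Use one fixed encouragement script, at set times in the test, in both arms and at every fitness test, including baseline.
- Where existing staffing allows, have the 6- and 12-month tests run by laboratory staff who are not that participant's counselor and are not shown the arm.
- Report RER and peak heart rate by arm at each visit as a check on effort. The article already provides for RER as a peak criterion and for recording peak heart rate.

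The cost is procedure wording and some constraint on the rota; visits and sample size do not change. Participants will sometimes reveal their arm, and the script still helps when they do.

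**For tests already completed:** do not reword how they were conducted. Report who ran them, whether those staff knew the arm and whether any script was used; compare the effort measures by arm; and state the limitation alongside the primary result. This costs a short passage and one table of data that the test should already have captured. Similar effort measures in the two arms would be reassuring, though not proof that there was no bias.
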